**Methods:**

The children will be randomly allocated to four groups of 19 individuals: G1 - low-level laser; G2 - occlusal splint; G3 - placebo laser; and G4 - control (without bruxism). The BTS TMJOINT electromyography will be used to determine muscle activity and a digital gnathodynamometer will be used to measure bite force. Salivary cortisol will be analysed at baseline as well as one and six months after treatment. Two-way ANOVA will be employed and complemented by Tukey’s test.

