The frequency of bruxism is high in childhood, with prevalence rates ranging from 13.5 to 33% [14, 15] and this condition can cause harm to the stomatognathic system. Childhood bruxism is difficult to diagnosis and ideal treatment has not yet been established. Physical therapy is currently used to treat this condition and the most commonly employed methods are transcutaneous neuromuscular stimulation, microcurrent electrical neuromuscular stimulation, cryotherapy, ultrasound, infrared therapy, kinesiotherapy, massage therapy, acupuncture, low-level laser therapy (LLLT) and occusal splint usage [16, 17]. According to Solberg et al. [18], an occlusal splint reduces muscle activity and provides greater patient comfort. Occlusal splint usage seems to reduce tooth grinding, masticatory muscle activity and orofacial pain [19]. Although occlusal splints are widely employed for the treatment of bruxism, no specific strategy has been established for the cure of this condition. Thus, further studies are needed [18, 20].

LLLT is a non-invasive, low-cost treatment. The irradiation of trigger points constitutes effective treatment for orofacial pain as well as the reduction of swelling and hyperemia [21]. Acupuncture has also been successfully used for the treatment of bruxism, achieving a reduction in the activity of the masseter and anterior temporal muscles as well as a reduction of anxiety [22]. The stimulation of particular acupoints can alter blood circulation dynamics and promote muscle relaxation, thereby alleviating muscle spasms, inflammation and pain. Moreover, such stimulation leads to the release of hormones, such as cortisol and endorphins, thereby promoting an analgesic effect [23]. The stimulation of acupoints can be achieved with the use of needles, infrared irradiation, electrical current or laser [24]. The latter method is indicated for children because it is painless and has a shorter exposure time per acupoint [25–27]. However, the use of LLLT over acupoints has not yet been tested on children with bruxism. Therefore, the aim of the proposed study is to investigate changes in maximum bite force (measured using a gnatodynamometer) one and six months after low-level laser therapy over acupoints and occlusal splint usage compared to muscle hyperactivity at baseline in children. The secondary outcomes are the measure of pain (VAS scale), muscle activity (using the BTS TMJOINT® electromyograph) and salivary cortisol.

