### Randomisation and interventions

Randomisation will be performed using Microsoft Excel (version 2013). Seventy-six patients will be randomly allocated to the four groups. Randomisation will be in block form (groups of four patients).

Seventy-six opaque envelopes will be identified with sequential numbers (1 to 76) and each will contain information regarding the corresponding group following the established random order. The envelopes will be sealed until the time of treatment.

Patients will be allocated as follows:

Group 1 will receive low-level laser over acupoints; Group 2 will use an occlusal splint; Group 3 will receive placebo laser therapy over acupoints; and Group 4 (control group) will be composed of children without bruxism and will not receive any type of treatment. Parents/guardians will received guidance throughout the study. In G1, low-level laser (power: 70 mW; energy density: 1.675 mW/cm^2^; 12 points irradiated; 1 J per point for 20 s; 12 sessions; 12 J/session; twice a week) will be applied directly to the skin at six acupoints on each side, always by the same operator. In G2 and G3, the laser device will be positioned over the same points as in G1, but will be switched off.Group 1 – experimental (*n* = 19) – low-level laser therapy over acupoints;Group 2 –positive control (*n* = 19) – occlusal splint usage;Group 3 – control (*n* = 19) – placebo laser therapy over acupoints;Group 4 – control (*n* = 19) – children without bruxism (Additional file 2)

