The child will be seated comfortably in a room without noise or sound interference and positioned with the Frankfurt plane parallel to the floor. A total of twelve sessions of LLLT will be performed at a frequency of twice per week using a laser at wavelength of 786.94 nm with a conventional tip, energy density of 25 J/cm^2^, intensity of 1.675 mW/cm^2^, power of 70 mW, 1 J (J) per point for 20 s for a total of 12 J per session. Point application will be used in direct contact with the skin (spot area: 0.04 cm^2^) following the protocol suggested by Carvalho et al. [30] and Venezian et al. [21]. The Twin Flex Evolution® device (MM Optics) will be employed. A potentiometer will be used at the onset of the study to determine the effective mean power of the equipment and therapeutic doses applied during clinical use. The points irradiated are listed below with their respective explanations:IG-4 (Hegu) - has a direct and strong influence on the face, eyes, ears, nose and mouth. It is also used to calm the mind and relieve anxiety. This point is located in the patient’s hand at the base between the thumb and index fingerF-3 (Taichong) - exerts a profound soothing effect on the mind. Its soothing action is increased when combined with IG-4.This point is located in the patient’s feet at the base between the hallux and index toe.VB-34 (Yanglingquan) - is an important point to relax the tendons whenever there are muscle contractions. This point is located in the upper distal part of gastrocnemius muscle.E-36 (Zusanli) - indicated to treat irritability, depression, insomnia, tiredness, fatigue and headache. This point is located below the patella in the lateral portion of the tibia.ID-19 (Tinggong) - indicated to treat problems in the ear region. This point is located in the anterior part of the tragusBP-6 (Sanyinjiao) - this is one of the most important points, with a broad scope of action. It has a strong soothing action on the mind and is generally used to treat insomnia. This point is located in the proximal end of the medial malleolus, the distal margin of the tibia (Additional files 3 and 4).

The patients in G3 (placebo LLLT) will receive the same treatment as those in G1, with the same equipment and a pen that emits a red guide light and a sound, but does not emit energy. After 30 days of follow up, the volunteers in this group will receive complementary treatment for the control of bruxism for ethical reasons.

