### Study variables

All groups will be submitted to the evaluation of muscle activity using the BTS TMJOINT® electromyograph and the evaluation of bite force with a gnatodynamometer at baseline as well as one and six months after treatment. Salivary cortisol will be measured at baseline and after the therapeutic intervention.

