### Protocol for analysis of bite force

Bite force will be measured using a digital dynamometer (DMD model, Kratos Equipamentos Industriais Ltda, Cotia, SP, Brazil) adapted for oral conditions. This device is an electronic bite force meter composed of a bite fork and module with a digital display connected by a wire. The readings will be made in the region of the first molars in Angle Class I [33] and free of caries. The volunteer will receive prior orientation and training to become familiar with the device. Six readings will be made – three on the right side and three on the left side, alternating sides between readings. Each reading will last five seconds and will be separated by a one-minute rest period. Bite force will be evaluated prior to the onset of treatment, at the end of treatment and 30 days after the end of treatment. The results will be computed and analysed statistically.

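### At six months the placebo group (G3) has been given complementary bruxism treatment, so a six-month comparison with G3 is not placebo-controlled

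*Protocol article*

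**What the plan says.** G3 is defined under Randomisation and interventions as "Group 3 – control (*n* = 19) – placebo laser therapy over acupoints". The same section adds: "After 30 days of follow up, the volunteers in this group will receive complementary treatment for the control of bruxism for ethical reasons". This applies to the whole group, and the complementary treatment is not described.

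The assessment times are given in several places and do not agree:

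- **EMG, all groups** (Study variables): "at baseline as well as one and six months after treatment".
- **Bite force.** Study variables gives the same times as for EMG. The aim in the Background places it "one and six months after low-level laser therapy over acupoints and occlusal splint usage compared to muscle hyperactivity at baseline in children". The dedicated section, Protocol for analysis of bite force, says instead: "Bite force will be evaluated prior to the onset of treatment, at the end of treatment and 30 days after the end of treatment".
- **Salivary cortisol.** The Abstract says: "Salivary cortisol will be analysed at baseline as well as one and six months after treatment". Study variables has only baseline and a reading after the intervention, and the cortisol section gives the second reading as Day 50.
- **Pain** is rated before and after treatment.

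The Abstract plans two-way ANOVA with Tukey's test and does not name the two factors. Neither the Abstract nor Statistical analyses treats G3 differently at one and at six months.

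**The concern.** A placebo arm supports a placebo-controlled claim only while it stays on placebo. After the switch, G1 versus G3 compares laser with a sequence: placebo, then another treatment for the same condition. If that treatment works, the two groups move closer together. A laser effect that lasts to six months could then be reported as lost, or similar six-month values could be read as showing that laser does nothing.

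The same problem would enter the overall result if the ANOVA factors are group and time and the group effect, or the Tukey comparisons, are averaged over visits. That average would mix a true placebo contrast at one month with a treated-control contrast at six months.

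**Working it through.** **1. Is there another placebo group at six months?** No. G1 is active laser. G2 is the occlusal splint, listed as the positive control. G4 is children without bruxism, who get no treatment. G3 is the only placebo comparator among children with bruxism.

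**2. How long has G3 been off placebo by six months?** Twelve sessions at two per week take 12/2 = 6 weeks, or 42 days. If the 30 days run from the last session, the switch comes at about day 42 + 30 = 72. The six-month visit then follows the switch by about 6 − 1 = 5 months. If the 30 days were counted from the first session, the switch would fall at day 30, inside the 42-day course, and the one-month visit would be affected too. The article does not give the starting point.

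**3. Which outcomes are affected?**

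| Outcome | Six-month reading in G3? | Status of the point |
|---|---|---|
| EMG | Yes (Study variables); no conflicting schedule | Firm |
| Bite force | Yes in Background and Study variables; no in its own section | Depends on which prevails |
| Cortisol | Yes in the Abstract; no in Study variables and its own section | Depends on which prevails |
| Pain | No six-month reading stated | Not affected |

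**4. The plan's own sample-size figure.** Sample size calculation states 15.75 per group at α = 0.05 and 80% power, raised by 20% to 19. The formula for two means is n = 2(z₁₋α/₂ + z₁₋β)²/d², with d the difference in SD units.

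- d = 1: n = 2(1.960 + 0.842)²/1² = 15.70, close to 15.75. Solving for 15.75 gives d = 0.998.
- d = 0.2, a literal reading of the stated 20%: n = 392.4, which is not 15.75.
- Allowance: 15.75 × 1.2 = 18.9, rounded to 19.

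The stated figure thus fits a two-sided comparison with a difference of about 1 SD. The article gives no mean difference and no SD, so 1 SD is an assumption here. How 15.75 was reached is a separate question and does not affect this point.

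**5. What dilution could do (illustration).** Suppose the true laser-versus-placebo difference is d = 1 and the complementary treatment gives G3 a share s of it by six months. The remaining difference is (1 − s)d, and power ≈ Φ((1 − s)·d·√(n/2) − 1.960).

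For n = 16, √(16/2) = 2.828:

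- s = 0: 2.828 − 1.960 = 0.868, power 0.807
- s = 0.25: 2.121 − 1.960 = 0.161, power 0.564
- s = 0.50: 1.414 − 1.960 = −0.546, power 0.293
- s = 0.75: 0.707 − 1.960 = −1.253, power 0.105

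A two-sample t calculation at d = 1.024, which has 80% power at n = 16, gives 55.6%, 28.9% and 10.8% for the last three rows. At s = 1 only the 5% two-sided error rate is left. With all 19 per group, the normal approximation gives 0.869, 0.637, 0.338 and 0.117.

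**The case against.** The case on the other side has several parts, and much of it stands.

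- **The main objective does not involve G3.** The Background aim names laser and splint against baseline, and the Discussion gives laser versus splint as the main objective. No sentence announces a six-month G1–G3 test; that comparison is inferred from the visit schedule and G3's role as control. This stands. A reader might infer that the trial's main question is compromised, but G1 versus G2 is untouched by G3's later treatment.
- **The bite-force section stops at 30 days after treatment.** If that schedule governs and the 30 days of follow-up run from the end of treatment, with the reading taken first, G3 is still on placebo at every bite-force reading. This stands, and it makes the point conditional for the primary outcome. It does not help for EMG.
- **The direction of bias is not given.** A reader might infer that any six-month difference must be biased toward zero. That needs the complementary treatment to work and to move these outcomes as laser does. The article states its purpose but not what it is or what it achieves.
- **Randomisation still holds.** G1 versus G3 at six months remains a fair comparison of laser with placebo followed by treatment. It is a different question, not an invalid one.
- **Pooling over visits is not stated, and an analysis plan could separate the visits.** True. But no analysis plan can restore a placebo arm that the design has ended, so the label on the six-month comparison must still be corrected.

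**Conclusion.** The point holds in limited form. As written, the article ends G3's placebo status after 30 days of follow-up and still measures G3 at six months as a control. Any six-month comparison with G3 is against *placebo followed by complementary treatment*. This is firm for EMG. It holds for bite force if the Background and Study variables prevail over the bite-force section, and for cortisol if the Abstract prevails over Study variables and the cortisol section.

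The size of any dilution cannot be computed from the article. The fall from about 80% to 56%, 29% or 11% assumes an effect of about 1 SD, 16 per group, a simple two-group test rather than the planned ANOVA with Tukey's test, and arbitrary shares of benefit. It shows what could happen and is not an estimate for this trial.

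A reader might also infer that the trial has no placebo control at all. The article does not support that: the one-month contrast is intact if the 30 days run from the last session and the visit precedes the new treatment. This should be fixed, but it does not undermine the trial as a whole.

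**What to change.** - State that the placebo-controlled comparison, G1 versus G3, is the visit one month after treatment.
- Label six-month G3 data *placebo then complementary treatment* and make no six-month placebo-controlled claim.
- Do not pool G3 over visits in the group effect or in the Tukey tests.
- Keep the six-month G1 versus G2 comparison and the G4 reference. Neither is affected.
- Reconcile Background, Study variables and Protocol for analysis of bite force on whether bite force is read at six months. Reconcile the Abstract, Study variables and the cortisol section in the same way.
- Reconcile Randomisation and interventions with Study variables on when the 30 days of follow-up start and how that relates to the one-month visit. The provision to treat G3 is not in question here.

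The cost is wording in the protocol and the analysis description, with no added participants or visits. The trial gives up a six-month placebo-controlled claim, which its design cannot support in any case.

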### Study variables

All groups will be submitted to the evaluation of muscle activity using the BTS TMJOINT® electromyograph and the evaluation of bite force with a gnatodynamometer at baseline as well as one and six months after treatment. Salivary cortisol will be measured at baseline and after the therapeutic intervention.

### Protocol for electromyographic (EMG) evaluation of masticatory muscle and trapezius muscle

The electrical activity resulting from the activation of the masseter and temporal muscles as well as the descending fibres of the trapezius will be captured using a six-channel electromyograph (TMJOINT, BTS Engineering) with a bioelectric signal amplifier, wireless data transmission and disposable bipolar Ag/AgCl surface electrodes (Medical Trace®) measuring 10 mm in diameter. The EMG signal will be amplified with a 2000-fold gain and filtered within a frequency range of 20 to 450 Hz. Impedance of the equipment is >1015 Ω//0.2 pF and the common rejection mode ratio is 60/10 Hz 92 dB. The data will be captured and digitised at 1000 frames/s using the BTS MYOLA®52 software program. After cleaning the sites with 70% alcohol to diminish impedance between the skin and electrode [23], the self-adhesive surface electrodes will be attached over the belly of the muscle in the region with the most tonus (determined during moderate intercuspation) at a distance of 20 mm centre to centre, as suggested by the European Society Recommendations for Surface Eletromyography [23]. A reference electrode will be placed on the left wrist to impede the interference from outside noise.

The right and left masseter and anterior temporal muscles will be analysed under four conditions: i) at rest; ii) during maximum habitual intercuspation with a strip of Parafilm M® 40 between the molars for the collection of maximum voluntary contraction (MVC) of the muscles studied; iii) habitual chewing (isotonic contraction); and iv) maximum intercuspation (isometric contraction) without the Parafilm. Three readings will be made under each condition, with a two-minute interval between readings. The collection time will be 15 s for in the resting position, five seconds for MVC, 10 s for isotonic contraction and 10 s for isometric contraction [19, 31]. During the simulation of habitual chewing, a metronome set at 60 beats per minute will be used to standardise the process. The EMG signal captured during chewing will be rectified and normalised by the mean of the signal followed by the calculation of the root mean square (RMS) using a 500-ms moving window without overlap. The data will be normalised by the largest RMS obtained during MVC.

For the positioning of the electrodes on the descending fibres of the trapezius muscle, a point will be marked 2 cm lateral to the midpoint of the straight line between the posterior edge of the acromion and seventh cervical vertebra [19]. Prior to the readings, the participant will be instructed to sit in a chair with the shoulder and arm bare, back erect, knees flexed at 90° and feet apart for the collection of isometric MVC. Two non-elastic bands attached to each side of the base of the chair will be used to resist the movement of the raising of the shoulder during the reading. The volunteer will be instructed to raise the shoulders with maximum force for five seconds. The procedure will be repeated three times with a one-minute interval between readings. The highest value among the three readings will be used to normalise the EMG data of the descending fibres of the trapezius muscle. After a three-minute interval, the volunteer will be instructed to perform 90° abduction of both arms for 60 s, with the elbows completely extended and the forearms in pronation with the palms turned toward the floor. To monitor the position of the shoulder, two flexible rods positioned horizontally between the arms at a distance of 8 cm will be used to provide feedback of the tactile position [32].

Data processing of the EMG signals will be performed using specific routines developed in Matlab, version 7.1 (The MathWorks Inc., Natick, Massachusetts, USA).

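### As written, the chewing EMG signal is divided by its own mean, which cancels chewing amplitude before the MVC normalisation is applied

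*Protocol article*

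**What the plan says.** The section on EMG evaluation in the protocol article has the masseter and anterior temporal muscles recorded at rest, in a maximal clench on Parafilm (the MVC reference), in habitual chewing, and in a maximal clench without Parafilm.

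For chewing, the signal is to be "rectified and normalised by the mean of the signal followed by the calculation of the root mean square (RMS", with the RMS computed "using a 500-ms moving window without overlap". The next sentence adds: "The data will be normalised by the largest RMS obtained during MVC".

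The same section gives a 20 to 450 Hz filter, sampling at 1000 per second, and recording times of "five seconds for MVC, 10 s for isotonic contraction and 10 s for isometric contraction". Chewing is paced: "a metronome set at 60 beats per minute will be used to standardise the process".

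The step involving the mean is stated for chewing only. None is stated for rest or for "iv) maximum intercuspation (isometric contraction) without the Parafilm". Trapezius EMG is normalised only by the highest of three maximal readings. The section on occlusal contacts adds total masseter and temporal activity as an area over time. The end of the Background makes bite force the aim and muscle activity a secondary outcome.

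**The concern.** The mean of a rectified EMG signal is its average amplitude. Dividing the signal by that mean sets its average level to 1 for every child at every visit, so the quantity of interest is lost before the RMS is taken. Dividing next by the MVC RMS puts a unitless number over one in signal units, and the result is not chewing activity as a share of maximum.

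The trial studies muscle hyperactivity, and the Discussion links the chosen acupoints to muscle relaxation. A lower level of activity during chewing is one of the changes this index would be expected to detect. Under the written rule, two visits that differ only in chewing level give the same value.

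**Working it through.** The plan states no figure for this index, so there is nothing to reproduce. The check is algebra, illustrated by simulation.

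**Algebra.** Let the chewing signal be A·s(t), with amplitude A and shape s(t), and let M be the largest MVC RMS.

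1. Rectify and divide by the mean: |A·s| / mean|A·s| = |s| / mean|s|. A has dropped out.
2. Take the windowed RMS and divide by M: index = RMS(|s| / mean|s|) / M. This depends on shape and on 1/M, not on A.
3. With MVC normalisation alone: index = A·RMS(|s|) / M, which is proportional to A.

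The order of rectifying and dividing does not matter. If the divisor is the mean of the unrectified signal, A still cancels, and the divisor is close to zero after a 20 to 450 Hz filter.

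**Simulation.** From the protocol: 10 s of chewing at 60 per minute, 5 s of MVC, 1000 samples per second, 500-ms windows without overlap. Assumed: the amplitudes, a half-sine burst envelope filling 40% of each cycle, and averaging over the windows.

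| Chewing amplitude | MVC amplitude | Burst share of cycle | Written rule | MVC normalisation only |
|---|---|---|---|---|
| 200 | 200 | 0.4 | 0.00721 | 0.347 |
| 100 | 200 | 0.4 | 0.00721 | 0.174 |
| 70 | 200 | 0.4 | 0.00721 | 0.122 |
| 50 | 200 | 0.4 | 0.00721 | 0.087 |
| 100 | 140 | 0.4 | 0.01030 | 0.248 |
| 100 | 200 | 0.2 | 0.00895 | 0.123 |

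- **Amplitude.** A fall from 100 to 70 changes the written index by 0%. With MVC normalisation only, it falls by 30% (0.122/0.174 = 0.70). With additive noise of 3 units, halving the amplitude from 100 to 50 moves the written index only from 0.00717 to 0.00708, about 1%.
- **Burst shape.** Halving the burst share raises the written index by 24% (0.00895/0.00721 = 1.24). The index normalised by MVC only falls by 29% (0.123/0.174 = 0.71). The written index can therefore move against the activity level.
- **MVC.** A fall from 200 to 140 raises both indices by 43% (200/140 = 1.43).

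**Other readings.** If the MVC signal is also divided by its own mean, both amplitudes cancel and the index is 1.158 in every row with a burst share of 0.4. If the mean of the raw signal is subtracted before rectification, amplitude is kept: 0.174 at amplitude 100 and 0.087 at 50.

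**The case against.** The strongest reply is that the phrase is a loose description of offset removal. The text speaks of the mean of the signal, not of the rectified signal. Rectifying before an RMS is redundant, since squaring removes the sign, which suggests a condensed account. The Matlab routines are not shown. If the mean is subtracted, amplitude survives.

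That reading is possible, but the document points the other way. The next sentence, and the trapezius paragraph, use the same verb for scaling to a reference value. The 20 to 450 Hz filter already removes an offset. The redundancy cuts both ways too: rectification serves a purpose here only if the mean is taken from the rectified signal. Even if subtraction was intended, the sentence does not say so and needs correcting.

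A second reply concerns reach, and it stands. A reader might infer that the trial's muscle-activity outcome cannot show a change. The document does not support this: the mean step is written for chewing only, and the other EMG measures carry no such step. A reader might also infer that the index varies only with 1/MVC, but it responds to burst shape as well.

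Nor is the inverse movement with MVC caused by this error. Any MVC-normalised index behaves that way, and the 43% rise above appears equally under the corrected rule. The document also nowhere states that clenching strength is expected to change.

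**Conclusion.** The point holds for the chewing index. On the natural reading of the text as division, the index cannot show a uniform rise or fall in chewing activity of any size. What remains is burst shape and the inverse of MVC, in units that are not a percentage of MVC. The cancellation is exact and does not depend on the assumed amplitudes. The sizes quoted for burst shape and noise do depend on the assumed signal.

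The conclusion rests on the mean step being a division, which is the better-supported reading but not the only one. It concerns one condition of a secondary outcome. The rest, isometric, trapezius and area-over-time measures, and bite force, are not shown to be affected. It should be corrected, but it does not threaten the trial's main comparison.

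**What to change.** In the EMG section, delete the clause that normalises the chewing signal by its mean. If offset removal was meant, state instead that the mean of the raw signal is subtracted before rectification. Then compute the RMS in signal units and divide once by the largest MVC RMS of the same muscle at the same visit. Check that the Matlab routine does the same.

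The cost is one sentence and one line of code, with no new recordings or visits. If the raw signals are kept, any chewing data already processed can be recomputed.

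Optionally, tabulate the MVC RMS in signal units by group and visit, so that a shift in the denominator can be seen. This helps with reading any MVC-normalised index and is not part of the error.
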